### Modalities of outcome evaluation

The GOS score is determined on day 90 (±7 days) during a structured phone interview conducted by an independent assessor blinded to the allocation group (Table 2).

**Table 2 Tab2:** Categories of the Glasgow Outcome Scale Adapted from Jennett B et al.

Category	Classification	Description
1	Death	Patient is certified dead
2	Vegetative state	Patient is unable to interact with the environment *Patients who show no evidence of meaningful responsiveness. This non*-*sentient state must be distinguished from other conditions of wakeful, reduced responsiveness*–*such as the locked*-*in syndrome, akinetic mutism, and total global aphasia. Vegetative patients breathe spontaneously, have periods of spontaneous eye*-*opening, may follow moving objects with their eyes, show reflex responses in their limbs (to postural or painful stimuli), and they may swallow food placed in their mouths*
3	Severe disability	Patient is unable to live independently but can follow commands *This indicates that a patient is conscious but needs the assistance of another person for some activities of daily living every day. This may range from continuous total dependency to the need for assistance with only one activity*
4	Moderate disability	Patient is capable of living independently but unable to return to work or school *Such a patient is able to look after himself at home, to get out, and about to the shops and to travel by public transport. However, some previous activities, either at work or in social life, are now no longer possible by reason of either physical or mental deficit*
5	Mild or no disability	Patient is able to return to work or school *This indicates the capacity to resume normal occupational and social activities, although there may be minor physical or mental deficits. However, for various reasons, the patient may not have resumed all his previous activities and in particular may not be working*

When possible, on day 90 (±7 days), patients return to the centre where they were included, for an evaluation by a neurologist including an interview and determination of the GOS score by structured interview, MMSE score, and FIM score. The patient brings an MRI of the brain and conventional EEG. The neurologist records any recurrent CSE episodes since randomisation; frequency of any recurrent seizures, as well as their type and associated symptoms; nature and dosage of antiepileptic drugs; and other treatments.

### Independent data safety monitoring board (DSMB)

The independent data safety monitoring board (DSMB) is composed of three physicians ([name], Neurology Department, Saint Denis Hospital, Saint Denis, France; [name], Intensive Care Unit, Pitié Salpétrière University Hospital, France; and [name], Intensive Care Unit, Limoges University Hospital, Limoges, France) and one biostatistician ([name], Urgences-Samu 93, Avicenne University Hospital, Bobigny, France) not otherwise involved in the trial. The DSMB assesses the safety data whenever complete 90-day follow-up data become available for 45 additional patients. For each of these safety analyses, the DSMB has access to blinded results on 28-day mortality, ICU discharge mortality, and 90-day GOS scores. The DSMB also evaluates all reported serious adverse events.

### End of the trial

Each patient is in the trial for 90 days. Premature study withdrawal is considered if requested by the patient or next of kin. Patients who are lost to follow-up or do not receive the randomly assigned treatment are not classified as prematurely withdrawn from the trial. Prematurely withdrawn patients are not replaced but undergo the procedures scheduled for the last visit, to the extent possible. Furthermore, the reason for premature withdrawal is recorded in both the CRF and the source document.

### Sample size

The working hypothesis for this randomised controlled trial is that, compared to standard care alone, standard care combined with therapeutic hypothermia increases the proportion of patients with a good 90-day outcome defined as a GOS score of 5. Assuming that 40 % of patients will have a GOS score of 5 on day 90 in the standard care group [4] and that this percentage will increase by 20 % (to 60 %) with therapeutic hypothermia, with a 5 % two-sided type I error rate, 90 % power, and a single interim analysis performed according to the O’Brien-Fleming method, 135 patients are needed in each group (270 patients in all).

### Statistical methods

The statistical analysis will follow the intention-to-treat approach, with each patient being analysed as a member of the group assigned by randomisation, regardless of subsequent events. In addition, any missing value will be replaced by the previous value according to the last value carried forward method. A sensitivity analysis of missing values will be carried out, using multiple imputation by chained equations (MICE). Comparisons of the two groups will routinely consider a possible centre effect.

A statistical analysis report will be written to describe all the findings according to CONSORT statement recommendations, taking into account the specific features of the trial. Any change in the analysis plan will be justified in the final report.

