**Fig. 2 Fig2:**
[figure not shown]
Eligibility criteria, inclusion, randomisation, and treatment implementation modalities in each arm of the trial

**Table 1 Tab1:** HYBERNATUS trial flow chart

	Inclusion	Day 0	Day 1	Day 2 Day 7 Day 14 Day 28	ICU discharge	Hospital discharge	Day 90 (±7 days)
Eligibility: check inclusion and non-inclusion criteria	X						
Patient/next of kin information and consent	X						
Randomisation (within 8 h after CSE onset)		X					
Standardised anticonvulsant treatment		X					
Brain imaging and other aetiological investigations		X					
Therapeutic hypothermia (in the intervention group)		X	X				
Core temperature monitoring (every 4 h)		X	X				
Continuous EEG monitoring		X	X				
30-min continuous EEG extract (centralised reading)		X	X				
Clinical and laboratory monitoring		X	X	X	X		
Serious adverse event reporting		X	X	X	X	X	X
Glasgow Outcome Scale (GOS) score evaluation					X	X	X^1, 2^
Standard EEG							X^2^
Brain MRI							X^2^
MMSE score							X^2^
FIM scale score							X^2^
Neurological evaluation							X^2^

^1^By phone interview in all cases

^2^Neurologist visit, if feasible

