### Other general measures

In both groups, a standardised neurological examination is performed every 4 h by the physicians and nurses in charge of the patient (GOS score, pupillary reflex, corneal reflex, cough reflex, spontaneous breathing, abnormal movements, focal neurological signs). Core body temperature is monitored continuously using an oesophageal probe and recorded every 4 h during the first 48 h after randomisation.

Patients are routinely screened for propofol infusion syndrome via measurements of arterial blood gas, serum lactate, serum triglycerides, and serum creatine phosphokinase every 8 h during the first 48 h after randomisation.

The prevention of secondary brain injury relies on temperature control to avoid hyperthermia in the control group and, after rewarming, in the therapeutic hypothermia group; glucose control between 0.8 and 1.4 g/L, maintenance of normoxia with PaO_2_ ≥ 80 mmHg and SaO_2_ ≥ 95 %; maintenance of normocapnia with PCO_2_ between 35 and 40 mmHg; 45° head-of-bed elevation; maintenance of mean arterial pressure between 70 and 90 mmHg; and serum sodium control between 138 and 142 mmol/L. Special attention is paid to the occurrence of aspiration pneumonia, and three samples for blood cultures are taken routinely within 24 h after randomisation.

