### Data collection and follow-up

The following baseline characteristics are recorded at admission: age, sex, date and time of ICU admission, McCabe score and Knaus score, and pre-existing comorbidities. The Simplified Acute Physiology Score II is computed 24 h after ICU admission.

The study protocol also requires collection of the following data:Description of the CSE: circumstances of onset, date and time of onset and of seizure control, clinical features of seizures, pre-hospital and hospital providers and timing of anticonvulsant and supportive treatments, results of aetiological investigations (brain CT, lumbar puncture, MRI, laboratory tests including toxicological screen), aetiological diagnosis, type and dosage of antiepileptic drugs, and date and start and stop times of continuous EEG monitoring;Data related to ICU and hospital management: description of the acute disease; description of organ failures according to the Logistic Organ Dysfunction score (at inclusion and on days 0, 1, 2, 7, 14, and 28); use of mechanical ventilation, inotropic support, and/or renal replacement therapy; vital and functional status at ICU and hospital discharge according to the GOS; and cause of death (treatment limitation decision, refractory SE, and/or ICU complications);Data related to therapeutic hypothermia: modalities of induction and maintenance; core temperature every 4 h during the first 48 h; serum levels of creatine phosphokinase, triglycerides, and electrolytes; arterial lactate and blood gas levels; electrocardiogram; occurrence of aspiration pneumonia; and results of blood cultures on samples taken within the first 24 h;Data related to outcomes: 90-day GOS score by structured phone interview and neurologist visit; description of functional sequelae; mini–mental state examination (MMSE) score; and Functional Independence Measure scale (FIM) score.

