### Study outcomes

#### Primary outcome

The primary outcome is GOS score determined by a structured interview lower than 5 on day 90.

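### Last value carried forward as the main missing-data rule replaces a missing day-90 GOS by an earlier discharge GOS, which can bias the primary comparison by an amount the documents do not let us fix

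*Protocol article*

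**What the plan says.** The Statistical methods section sets an intention-to-treat analysis in which "any missing value will be replaced by the previous value according to the last value carried forward method". The next sentence adds multiple imputation by chained equations as a sensitivity analysis. Nothing exempts the primary outcome.

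The endpoint is defined under Study outcomes: "The primary outcome is GOS score determined by a structured interview lower than 5 on day 90". Modalities of outcome evaluation says this score is obtained "during a structured phone interview conducted by an independent assessor blinded to the allocation group". The Blinding section gives that arrangement as the safeguard against evaluation bias in an open-label trial.

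The earlier scores available to carry forward are those at discharge. In Table 1 the row "Glasgow Outcome Scale (GOS) score evaluation" is marked at ICU discharge, hospital discharge and day 90. Data collection and follow-up likewise lists "vital and functional status at ICU and hospital discharge according to the GOS".

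End of the trial says that patients lost to follow-up are not classed as withdrawn, so they stay in the analysis with day-90 data missing. Sample size states no allowance for missing outcomes.

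**The concern.** The rule assumes that a patient's GOS does not change between discharge and day 90. The endpoint is cut at GOS 5, which Table 2 describes in these terms: "This indicates the capacity to resume normal occupational and social activities, although there may be minor physical or mental deficits". A score given on leaving the ICU or hospital is an uncertain stand-in for that capacity some weeks later.

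The rule also weakens the trial's protection against biased assessment. The day-90 interview is structured and blinded; the documents say neither of the discharge rating. For every patient with a missing day-90 score, a protected measurement is replaced by one with no such stated protection.

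Single imputation then treats the carried value as observed, so the standard error ignores the uncertainty of the replacement. For 90-day mortality, a literal application would count a patient discharged alive and then lost as alive on day 90.

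At stake is the main treatment estimate. If loss differs between arms, the type I error is at stake as well.

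**Working it through.** **Inputs from the protocol article.** GOS 5 on day 90 in 40% of controls and 60% with hypothermia; two-sided 5%; 90% power; one O'Brien-Fleming interim; 135 per arm (Sample size). The interim is after 135 of 270 patients (Interim analyses).

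**Reproducing the planned size.** The pooled two-proportion formula gives 130 per arm. The two-look O'Brien-Fleming inflation of 1.0071 gives 130 × 1.0071 = 130.9, so 131 per arm, within 3% of 135. The final critical value is 1.977 (nominal two-sided level 0.048).

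**Convention below.** SE = √{[p₁(1−p₁) + p₂(1−p₂)]/135} and power = Φ(difference/SE − 1.977). With nothing missing: SE = √(0.48/135) = 0.0596 and power = Φ(3.354 − 1.977) = 0.916.

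**Assumptions.** The documents give neither a missing rate *m* nor the relation of discharge to day-90 GOS. Two models bracket the answer.

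*Model 1 (severe).* Mortality is 20% in both arms and losses occur only among survivors. Day-90 GOS 5 among survivors is then 0.40/0.80 = 50% and 0.60/0.80 = 75%. A share *g* of 10–30% of the lost had GOS 5 at discharge, the same in both arms. Observed proportion = p − m × (survivor rate) + m × g, so the difference is 0.20 − 0.25m whatever *g* is.

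*Model 2 (milder).* Discharge and day-90 GOS are related: s = P(GOS 5 at discharge, given GOS 5 on day 90) and q = P(GOS 5 at discharge, given GOS below 5 on day 90). Observed proportion = (1−m)p + m[ps + (1−p)q], so the difference is 0.20 × [1 − m(1 − s + q)].

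**Equal loss, true effect 20 points.**

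| m | Model | Observed proportions | Difference (points) | Power |
|---|---|---|---|---|
| 3% | 1, g = 0.1 | 0.388 / 0.5805 | 19.25 | 0.894 |
| 5% | 1, g = 0.1 | 0.380 / 0.5675 | 18.75 | 0.878 |
| 5% | 2, s = 0.7, q = 0.05 | 0.3955 / 0.592 | 19.65 | 0.906 |
| 10% | 1, g = 0.1–0.3 | 0.36–0.38 / 0.535–0.555 | 17.5 | 0.83 |
| 10% | 2, s = 0.5, q = 0.05 | 0.383 / 0.572 | 18.9 | 0.883 |
| 10% | 2, s = 0.7, q = 0.05 | 0.391 / 0.584 | 19.3 | 0.895 |
| 15% | 1, g = 0.1–0.3 | 0.34–0.37 / 0.5025–0.5325 | 16.25 | 0.77–0.78 |

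**Like-for-like comparison.** Part of each power loss comes from the missing data and not from the rule.

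- Under Model 1, impute lost survivors from observed survivors of the same arm, with no other predictor. With r the survivor rate, the variance per arm is 0.64·r(1−r)/[135(0.80−m)] + 0.16·r²/135. At m = 10% this is 0.001989 + 0.001937, so SE = 0.0627 and power = Φ(0.20/0.0627 − 1.977) = 0.89. The carried value costs 0.89 − 0.83, about 6 points. At m = 15% the comparator is 0.87, a cost of about 9–10 points.
- Under Model 2 at m = 10%, dropping patients missing at random leaves 121.5 per arm: SE = √(0.48/121.5) = 0.0629 and power 0.886. The carried-forward figures of 0.883 and 0.895 are about equal to it.

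**Unequal loss.** Type I error = 1 − Φ(1.977 − d) + Φ(−1.977 − d), with d = |false difference|/SE, at a 40% rate in both arms.

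- Model 1, 5% against 15%: 0.38 against 0.34 (g = 0.1) or 0.39 against 0.37 (g = 0.3). The false difference is 4 or 2 points and type I error 0.102 or 0.061.
- Model 2, 5% against 15%: 1.7 points (s = 0.5, q = 0.05) or 2.7 points (s = 0.3, q = 0.02); type I error 0.057 or 0.072.
- Model 1, 3% against 5%: 0.4–0.8 points; type I error stays about 5%.
- With the true 20-point effect, Model 2 (s = 0.3, q = 0.02) gives 0.5382 − 0.3866 = 15.2 points when 15% of hypothermia and 5% of control patients are missing, and 0.5794 − 0.3598 = 22.0 points when the loss is reversed. The bias can therefore exaggerate the effect.

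**The case against.** The strongest reply is that the size is unknown and may be small. No missing rate is stated, and the design works against loss: Table 1 specifies a phone interview in all cases, the window is ±7 days, and a neurologist visit, when possible, also yields a structured GOS. At 3–5% balanced loss the shrinkage is about 1 point or less and power falls by about 1–4 points. Multiple imputation is prespecified and would reveal dependence on the carried values. All of this stands, and it limits the severity. It does not make the rule sound: the main analysis is fixed before the missing rate is known, and a sensitivity analysis does not replace the primary result.

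A reader might infer more than the documents support:

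- *That nearly every lost survivor is turned into a failure, because few reach GOS 5 at discharge and many recover later.* The documents give no discharge GOS distribution, and Table 2 defines GOS 5 by capacity, not by having resumed work.
- *That discharge falls at different times in the two arms.* This is stated nowhere.
- *That the rule itself cuts power from about 92% to 83% at 10% missing.* That compares it with complete data. Against a like-for-like analysis the cost runs from about 6 points to nothing.
- *That an acute-phase score could be carried forward, since Other general measures lists "GOS score, pupillary reflex, corneal reflex, cough reflex, spontaneous breathing" in the four-hourly examination.* Table 1 does not schedule that as an outcome, and the point does not need it.
- *That MMSE and FIM are biased by the rule.* They are scheduled only on day 90, so the rule has nothing to carry. It is inapplicable there, not biasing.

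**Conclusion.** The point holds as a bias problem of uncertain size. As written, the main rule puts an earlier rating, not stated to be blinded or structured, in place of the day-90 endpoint and treats it as observed. With similar loss in both arms the usual direction is towards no effect: at 10% missing, 0.7 to 2.5 of the planned 20 points are lost across the models tried. With unequal loss the direction is open. The type I error of about 6–10% needs the assumed threefold imbalance of 5% against 15%.

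These figures rest on assumed missing rates, an assumed 20% mortality under the severe model, and assumed links between discharge and day-90 GOS. The interval being too narrow follows from single imputation in principle; its size was not calculated. The plan should be changed, but the documents do not show that the primary result would be seriously distorted.

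**What to change.** Before any unblinded analysis, exchange the roles of the two methods for the day-90 GOS.

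1. Make multiple imputation by chained equations the primary approach. Keep known deaths as GOS 1. Include arm, centre, age stratum, seizure-duration stratum and the ICU- and hospital-discharge GOS in the imputation model.
2. Keep last value carried forward only as a labelled sensitivity analysis, beside a best-case/worst-case or delta-shift analysis.
3. State that being alive at discharge is not carried forward into 90-day mortality.
4. Report the number of missing day-90 scores by arm, since the size of the problem depends on it.

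No new data are needed: the method is already planned and the predictors are already collected. The cost is one of timing. According to the amendments and Trial status sections, the interim analysis took place in May 2013, enrolment is complete and analysis is under way. This would be a late change to the primary missing-data rule in an open-label trial. It has to be dated and justified in the final report, as the Statistical methods section already requires for any change to the analysis plan.

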#### Primary outcome

The primary outcome will be assessed by using logistic regression to compare the percentage of patients with a 90-day GOS score lower than 5 in the two study groups. If needed, the logistic regression model will be adjusted to allow a more accurate assessment of the effect.

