## Background

Convulsive status epilepticus (CSE) is a life-threatening emergency that requires on-scene antiepileptic treatment adjusted according to the treatment response [1]. Hospital mortality is about 20 % overall and reaches 40 % in patients with severe refractory CSE [2]. The morbidity associated with CSE is more difficult to evaluate, as adverse events are often erroneously attributed to the cause of CSE. In retrospective studies, Glasgow Outcome Scale (GOS) scores indicated neurological impairments in 28 % of patients after CSE and 54 % after refractory CSE [3]. In a prospective multicentre study, 50 % of CSE survivors requiring ICU admission had impaired 90-day functional outcomes defined as a GOS score <5 [4]. By multivariate analysis, factors independently associated with poorer outcomes were age, duration of motor seizures, focal neurological signs, and progression to refractory status epilepticus (SE) [4]. Some of these factors may be amenable to improvement and therefore may constitute therapeutic targets. Thus, outcomes may be improved by the rapid control of seizure activity (shorter seizure duration and prevention of refractory CSE and NCSE) and by treatment of the cause of CSE [5, 6].

Therapeutic hypothermia has shown both anticonvulsant and neuroprotective properties after SE in experimental studies. In rats, hypothermia at 32–34 °C decreased the incidence of both seizures and associated local and hippocampal neuronal damage [7–13]. In humans, therapeutic hypothermia has been described merely as an adjuvant treatment of super-refractory SE in adults and paediatric patients [14–17]. Finally, therapeutic hypothermia may also target some of the causes of status epilepticus such as ischaemic or haemorrhagic stroke [18–22] and subarachnoid haemorrhage [23–25]. Its use in patients with traumatic brain injury demonstrated conflicting results [26–30]. Thus, pathophysiological considerations and experimental data suggest a beneficial effect of therapeutic hypothermia in SE. Proof of such an effect in human patients has not been obtained [31, 32].

The main goal of the HYBERNATUS trial is to determine whether therapeutic hypothermia (32–34 °C) for 24 h has neuroprotective effects compared to standard care alone. HYBERNATUS is a multicentre, open-label, parallel-group, randomised, controlled trial in patients with CSE requiring admission to the intensive care unit (ICU) and mechanical ventilation.

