### Randomisation

Consecutive eligible patients are randomly allocated in a 1:1 ratio to one of the two treatment groups. The randomisation scheme involves permuted blocks and stratification on centre, age (≤65 or >65 years), and seizure duration (≤60 min or >60 min). Randomisation and concealment are ensured by using a secure, computer-generated, interactive, response system available at each study centre and managed by the biometrics unit of the Saint Louis University Hospital (Paris, France), which has no role in patient recruitment.

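### The primary logistic model should always include the age and seizure-duration strata used in randomisation; the plan adjusts only 'if needed' and gives no trigger or covariates

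*Protocol article*

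**What the plan says.** All references are to the protocol article.

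- **Statistical methods, Primary outcome.** The model is stated thus: "The primary outcome will be assessed by using logistic regression to compare the percentage of patients with a 90-day GOS score lower than 5". The comparison is between the randomised arms. On adjustment, the article then says: "If needed, the logistic regression model will be adjusted to allow a more accurate assessment of the effect." No covariate is named, and nothing says what would create the need or when it would be judged.
- **Statistical methods, opening paragraph.** "Comparisons of the two groups will routinely consider a possible centre effect." Age and seizure duration are not mentioned as model terms anywhere in the analysis sections.
- **Randomisation.** Permuted blocks with "stratification on centre, age (≤65 or >65 years), and seizure duration", the last cut at 60 minutes.
- **Background.** In an earlier prospective multicentre study, "factors independently associated with poorer outcomes were age, duration of motor seizures, focal neurological signs, and progression to refractory status epilepticus (SE"). The Sample size section cites the same study for the control-group rate.
- **Statistical methods, Secondary outcomes.** The primary-outcome method is carried over to the binary secondary outcomes, so the open clause goes with it.

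**The concern.** Stratified randomisation makes the arms alike on the stratification factors. If those factors predict outcome, the true variance of the treatment comparison falls. An unadjusted model does not know this, and its standard error still contains the between-stratum variation. The test is then somewhat conservative and some power is lost. Including the strata in the model recovers it.

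The design already settles which factors to include, so there is no need to be assessed. A conditional clause leaves two things unfixed in the analysis that decides the trial: which of several p-values is primary, and which odds ratio is estimated. In logistic regression the adjusted and unadjusted odds ratios are different quantities even when the arms are perfectly balanced. The O'Brien-Fleming boundary likewise presumes one defined test statistic at both looks.

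**Working it through.** **1. The plan's own figure.** Inputs from Sample size: GOS 5 in 40% of controls and 60% of treated patients, two-sided alpha 0.05, power 90%, one O'Brien-Fleming interim analysis.

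n per arm = [1.960·√(2·0.5·0.5) + 1.282·√(0.4·0.6 + 0.6·0.4)]² / 0.2² = (1.386 + 0.888)² / 0.04 ≈ 129.3, so 130.

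The two-look O'Brien-Fleming inflation factor is 1.0071 (final critical value 1.977): 130 × 1.0071 ≈ 130.9, so 131 per arm. The stated 135 per arm is slightly larger. Power at 135 per arm is Φ[(0.2·√135 − 1.386)/0.693] = Φ(1.354) ≈ 91.2%, or 90.9% at the final nominal alpha of 0.048. The sample size is sound without any adjustment.

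**2. Strata.** 11 centres × 2 × 2 = 44 strata, and 270/44 ≈ 6 patients per stratum on average.

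**3. Simulation of the analysis choice.** The design inputs are N = 270, 11 centres, 1:1 allocation, stratified permuted blocks, and poor outcome in 60% of controls and 40% of treated patients. The following are assumptions, because the article does not give them: block size 4, 35% aged over 65, 50% with seizures over 60 minutes, no centre effect, and the same prognostic odds ratio for each factor, varied from 1 to 4. There were 4,000 trials per setting, with Wald tests at 1.96 and no interim look. The Monte Carlo standard error of a 5% rate is √(0.05·0.95/4000) ≈ 0.35 points. 'Best of four' takes the most significant of four models: no covariate, age, duration, both.

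| Prognostic OR | Type I error, unadjusted | Type I error, adjusted | Type I error, best of four | Power, unadjusted | Power, adjusted | Gain (points) | Treatment OR, unadjusted | Treatment OR, adjusted |
|---|---|---|---|---|---|---|---|---|
| 1 | 5.27% | 5.35% | 5.50% | 91.13% | 91.20% | 0.1 | 0.44 | 0.44 |
| 1.5 | 4.28% | 4.52% | 4.62% | 91.17% | 91.85% | 0.7 | 0.44 | 0.43 |
| 2 | 4.35% | 5.00% | 5.58% | 91.40% | 92.80% | 1.4 | 0.44 | 0.42 |
| 3 | 3.50% | 4.55% | 5.03% | 92.23% | 94.13% | 1.9 | 0.44 | 0.39 |
| 4 | 3.87% | 5.65% | 5.90% | 92.03% | 95.07% | 3.0 | 0.44 | 0.37 |

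A separate simulation with 55% in the long-seizure stratum and odds ratios of 2 to 4 gave unadjusted type I error 4.2% to 4.8%, adjusted 5.0% to 5.5%, a power gain of about 1.4 to 2.5 points, and best-of-four type I error 5.2% to 5.9%.

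**4. The odds ratio.** The planning proportions imply a marginal odds ratio for poor outcome of (0.4/0.6)/(0.6/0.4) = 0.667/1.5 = 0.44. The unadjusted model estimates this. The adjusted model estimates a conditional odds ratio that moves away from 1 as the strata become more prognostic: 0.42, 0.39 and 0.37 at prognostic odds ratios of 2, 3 and 4. The underlying 60% and 40% are the same throughout.

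**The case against.** The strongest defence is that a journal article condenses the plan and that covariate lists usually sit in the SAP, which is not shown. A sentence that permits adjustment does not contradict an SAP that fixes it. That would answer a complaint about missing detail. It does not fully answer this point, because the article states a rule and the rule is conditional on an undefined need. The promise in Statistical methods to justify changes to the analysis plan does not help either, since adjusting and not adjusting both comply with the sentence as written.

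Other parts of the defence stand and limit the point:

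- A reader might infer that adjustment is to be decided after the data are seen. The article gives no timing, and the need could be judged blind to allocation.
- A reader might infer that age and seizure duration are excluded. No covariate is named, so none is excluded; they are simply not committed to.
- A reader might infer that the primary test is invalid, underpowered or open to serious p-value selection. The unadjusted test errs on the conservative side and has about 91% power. Best-of-four selection reaches at most about 5.9%, where the prespecified adjusted model itself showed 5.65%; the difference is small against Monte Carlo error.
- The prognostic factor in the Background is duration of motor seizures, while the stratum is seizure duration dichotomised at 60 minutes. Seizures may still be ongoing at randomisation, so the two are related but not identical.
- Open-label delivery adds little, since the day-90 GOS is assessed by interviewers blinded to allocation.
- The Background gives no effect sizes, and a random centre effect was not part of the simulations.

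**Conclusion.** The point holds as an improvement that costs nothing, not as a defect that undermines the trial. The primary model is left conditional where the design already dictates what belongs in it.

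For assumed prognostic odds ratios of 2 to 4, leaving the two strata out gives a type I error of about 3.5% to 4.8% and loses about 1 to 3 points of power. At 1.5 or less the loss is under 1 point. These figures rest on assumed prevalences, block size and odds ratios, and on no centre effect. The sample size is unaffected.

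The consequence for interpretation is at least as important: until the model is fixed, a reader cannot tell whether the primary odds ratio is marginal (about 0.44 under the planning assumptions) or conditional (about 0.37 to 0.42).

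**What to change.** Delete the conditional sentence and replace it with wording such as: The primary analysis is a logistic regression of day-90 GOS below 5 on treatment, age stratum (≤65 or >65 years) and seizure-duration stratum (≤60 or >60 min), fitted regardless of observed imbalance, with centre handled by [one named method, for example a random effect]. The adjusted odds ratio and a standardised risk difference, each with its confidence interval, will be reported; the unadjusted analysis is supportive.

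The standardised risk difference keeps the result on the scale of the 40% and 60% used for the sample size. Because the random effect was not simulated, the chosen centre method should be checked for stability with 11 centres and 270 patients before it is fixed.

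The cost is one sentence. The strata are known for every randomised patient, so no new data are needed. Timing does matter: the article reports the interim analysis in May 2013, enrolment completed in January 2015 and analysis ongoing. The change should therefore be dated and documented before comparative results are examined, with a note of which model the interim analysis used. If the SAP already fixes these covariates, it is enough to say so and correct the article's wording. The same wording should carry over to the binary secondary outcomes.
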